### Measures

#### Patient outcomes

While the survey battery assesses symptoms, the measures mostly target functioning, recovery, and impacts that are applicable to both SST- and CBSST-Peer. We will use a multidimensional battery of functional outcomes: (1) self-report (Independent Living Skills Survey (ILSS)), (2) interviewer-rated (Abbreviated Quality of Life Scale (A-QLS); Brief Psychiatric Rating Scale (BPRS); Clinical Assessment Interview for Negative Symptoms (CAINS)), and (3) objective-indicator (Psychosocial Rehabilitation (PSR) Toolkit) measures of functioning that are impacted by both social and cognitive skills. See Table 1 for a complete list and description of patient outcome measures. We selected the ILSS (Table 2) as the primary outcome because it has been the primary outcome measure in prior CBSST studies that demonstrated the efficacy of CBSST in improving social and cognitive skills. We also focus on the patient experience of recovery because it is now viewed as critical and yet relatively independent of the traditional view of clinical change. Hence, studies of peer specialists as a recovery-promoting intervention must consider outcomes designed to capture a patient perspective, beyond those narrowly applied to traditional clinical domains (e.g., symptoms). In addition, we include a measure tied to both the SST- and CBSST-Peer interventions itself—the Comprehensive Modules Test (CMT)—to assess how well the veterans learn the social and cognitive content and can apply it to change their defeatist attitudes.

**Table 1 Tab1:** Measures collected at baseline, 10 weeks, 20 weeks, and 32 weeks

Measure	Brief description
**Interview measures**	
**Abbreviated Quality of Life Scale (A-QLS)**	The A-QLS [19] is a 10-min semi-structured interview administered by a trained RA that measures subjective and objective aspects of functioning on 8 items in the past 4 weeks.
**Brief Psychiatric Rating Scale (BPRS)**	Assessed via clinical interview and subjectively rated by trained interviewers, the 24-item BPRS total score will be used to measure global psychopathology. The four BPRS positive symptom items—conceptual disorganization, suspiciousness, hallucinatory behavior, and unusual thought content—will be used to measure positive psychotic symptoms [20].
**Clinical Assessment Interview for Negative Symptoms (CAINS)**	Assessed via clinical interview and subjectively rated by trained interviewers, the 13 CAINS items are rated 0 (no impairment) to 4 (severe deficit) measuring the two negative symptom factors: expression and Motivation and Pleasure (MAP) across social, vocational, and recreational domains [21].
**Comprehensive Modules Test (CMT)**	The CMT is a 15-min interview assessing mastery of the content in the 2 CBSST modules and has been used in all prior CBSST trials. Questions with vignettes were developed to assess mastery of thought challenging (max = 11) and social communication (max = 11) skill knowledge. The CMT total score (max = 22) will be used.
**Psychosocial Rehabilitation (PSR) Toolkit**	The PSR Toolkit [22] is a 10-min interview used to collect information on employment, educational activity, and residential situation. In this brief interview, status in each functioning domain is rated on a progressive scale, ranging from the absence of meaningful functioning in the domain to fully independent functioning.

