CBSST [6] was developed by combining techniques derived from cognitive behavioral therapy (CBT) and social skills training (SST), including thought challenging, role-playing of communication skills, and problem-solving training, into a unique intervention that enhances daily role functioning. CBSST is a recovery-oriented psychosocial rehabilitation intervention that helps patients with SMI set goals, corrects errors in thinking, and builds communication skills to improve social functioning [7]. CBSST studies have demonstrated improved functioning, negative symptoms, and defeatist attitudes among individuals with schizophrenia and psychosis [7–13]. In these studies, CBSST was delivered by masters- or doctoral-level therapists, which limits how widely the intervention can be delivered.

Testing CBSST delivery by peer specialists provides several benefits. If effective, more providers will be able to deliver the intervention in a clinical setting, which meets SAMHSA’s third focus area. Additionally, peer specialists have the unique opportunity to use their lived experience while delivering the intervention which can enhance engagement among participants. Furthermore, this structured interface with SMI participants provides peer specialists with an ideal format to assist participants with achieving and maintaining recovery while improving functioning.

A recent pilot study using peer specialists to deliver CBSST showed improvement in outcomes among participants with SMI (*n* = 12) and demonstrated the ability of the peer specialists to deliver CBSST with high fidelity [14]. This study is the next step to examining the effectiveness of CBSST among individuals with SMI while also assessing implementation considerations in typical clinical settings. This study tests the effectiveness of peer specialists delivering CBSST (called CBSST-Peer) compared with SST-Peer and usual care among a population of veterans with SMI. Social skills training (SST) is another curriculum that targets some of the same social skills as CBSST but does not target errors in thinking (the “cognitive” in CBSST). Two meta-analyses of 49 SST clinical trials of patients with schizophrenia show that SST can improve basic conversation skills and community functioning [15, 16]. The following specific aims were developed based on the results of the pilot study.

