### Social skills training-peer condition

These groups will run according to the Bellack et al. model [30] used in VA’s national dissemination of SST. Peer specialists will receive the standard training that licensed independent practitioners (LIP) receive (peer specialists also are trained in SST, but current VA policy states they cannot deliver SST unless paired with an LIP). Similar to CBSST, these groups will use behavioral rehearsal role-play to improve communication and interaction skills. However, an important difference is that these groups will not include any cognitive training. There is flexibility in how long these groups run; however, to make the groups equivalent, we will make these groups last the same 20-week period.

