##### Aim 1: Effectiveness analysis and hypothesis

Analyses will test our hypothesis that veterans in CBSST-Peer will have superior functioning, recovery, attitude, and skill knowledge outcomes during treatment and follow-up relative to veterans in SST-Peer or TAU, and further that veterans in SST-Peer will have superior outcomes relative to TAU. Secondarily, we will apply all analyses to the symptom measures and explore the impact of gender and racial/ethnicity status where sample size allows. Analyses will follow the same pattern for all the above assessments. We will examine scores obtained at weeks 10 (mid-intervention), 20 (end-of-intervention), and 32 (post-intervention follow-up) as the outcome in HLM, with treatment condition included as a time-invariant covariate, and random intercepts for person and random slopes for time. All available data will be included in accordance with maximum-likelihood estimation procedures with data assumed missing-at-random, an assumption that will be tested with baseline clinical and demographic data. Preliminary analyses will examine potential baseline differences between the three conditions. Relevant covariates including treatment attendance, baseline symptom severity (via BPRS, CAINS), care services, and medications received (standard variables from the PSR toolkit), and demographic variables will be tested and included in the overall model according to model fit. The primary analysis will compare CBSST Peer to SST-Peer and TAU with independent contrasts in the HLM model of all post-baseline time points, to directly test the primary hypothesis that CBSST-Peer has superior outcomes than the other treatments (we will also compare SST-Peer to TAU). As compared to the group by time interaction, this test typically has greater power and is less susceptible to sample-specific artifacts (e.g., regression to the mean, variability in change over time). However, we also wish to examine the degree of change in outcomes over time in CBSST-Peer vs SST-Peer vs TAU. Thus, we will conduct additional analyses to test the treatment condition × time interaction, to examine the question of whether CBSST-Peer has greater improvement in outcomes over time than the other treatments.

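### The CMT total cannot show whether CBSST-Peer or SST-Peer teaches skills better, because half its points test thought challenging, which SST-Peer is designed not to teach

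*Protocol article*

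**What the plan says.** Table 1 of the protocol article describes the instrument: "The CMT is a 15-min interview assessing mastery of the content in the 2 CBSST modules". It has two equal parts, "mastery of thought challenging (max = 11) and social communication (max = 11) skill knowledge", and the table then fixes the score to be analysed: "The CMT total score (max = 22) will be used".

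Under Patient outcomes, the CMT is introduced with the words "we include a measure tied to both the SST- and CBSST-Peer interventions itself". The stated purpose is to see how well veterans learn both the social and the cognitive material.

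On the content of the comparator, the Background says that SST "targets some of the same social skills as CBSST but does not target errors in thinking". The section on the SST-Peer condition adds that "an important difference is that these groups will not include any cognitive training".

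The Aim 1 hypothesis is that CBSST-Peer will have "superior functioning, recovery, attitude, and skill knowledge outcomes during treatment and follow-up relative to veterans in SST-Peer or TAU", and that SST-Peer will in turn exceed TAU. On the method, the same section says: "Analyses will follow the same pattern for all the above assessments". So CBSST-Peer vs SST-Peer, CBSST-Peer vs TAU and SST-Peer vs TAU are all to be tested on the CMT total, over all post-baseline visits. The article mentions no subscale analysis.

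**The concern.** The chosen score conflicts with the design of the comparator. Half the points cover material that one of the two class arms deliberately leaves out. A CBSST-Peer lead on the total may mean that its participants learned skills better, or only that they were taught something the others were not. The total does not distinguish the two.

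Skill knowledge is one of four domains named in the Aim 1 hypothesis, so a positive result would probably be reported as support for CBSST over SST. The total could also conceal the opposite finding on common ground. CBSST-Peer gives one 10-class module to social skills, whereas SST-Peer runs for 20 weeks with no cognitive content. A social-communication advantage for SST-Peer could be outweighed by the thought-challenging points.

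SST-Peer vs TAU suffers in the other direction. Neither arm is taught thought challenging by the study, so half the score adds mostly noise to that contrast.

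**Working it through.** **The plan's own figure.** 11 + 11 = 22, as Table 1 states. The share of points on thought challenging is 11/22 = 50%.

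**Content set side by side.**

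| CMT part | Points | Taught in CBSST-Peer | Taught in SST-Peer |
|---|---|---|---|
| Thought challenging | 11 | Yes (Cognitive Skills Module) | No |
| Social communication | 11 | Yes (Social Skills Module) | Yes, in part: SST shares some of these skills |

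**How far this could carry the total.** The article gives no CMT standard deviation, effect size or subscale correlation, so these values are assumptions:
- d_tc: CBSST-Peer minus SST-Peer on thought challenging, in subscale SDs
- d_sc: the same for social communication
- rho: correlation between the subscales, which are taken to have equal SDs

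From the article: 252 participants in three arms (84 per arm), 20% dropout (84 × 0.8 = 67), two-sided alpha 0.05.

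Formulas: d_total = (d_tc + d_sc) / √(2(1 + rho)). The probability of a significant result favouring CBSST-Peer is Φ(d_total × √(n/2) − 1.96), for one time point.

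*No difference in social communication (d_sc = 0), rho = 0.5:*

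| d_tc | d_total | n = 67 | n = 84 |
|---|---|---|---|
| 0.3 | 0.17 | 0.17 | 0.20 |
| 0.5 | 0.29 | 0.39 | 0.46 |
| 0.8 | 0.46 | 0.76 | 0.85 |
| 1.0 | 0.58 | 0.92 | 0.96 |

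For d_tc = 0.8 and rho from 0.3 to 0.7, the probability is 0.82 to 0.71 at n = 67. On the social communication subscale alone, the probability in this direction would be the nominal 0.025.

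*SST-Peer better on social communication, d_tc = 0.8, rho = 0.5:*
- d_sc = −0.3: d_total = 0.5/1.732 = 0.29, probability 0.39 at n = 67. The total still points to CBSST-Peer although SST-Peer is ahead on the shared half.
- d_sc = −0.5: d_total = 0.3/1.732 = 0.17, probability 0.17.
- d_sc = −0.8: d_total = 0, probability 0.025. The advantage disappears only when the social deficit equals the cognitive gain.

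*Effect of pooling week 10.* The contrast uses weeks 10, 20 and 32 together. Assume a 3-point lead on the total at weeks 20 and 32 and none at week 10. The mean lead is (0 + 3 + 3)/3 = 2 points. At n = 67, with an assumed total-score SD of 4, 5 or 6:

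| Mean lead | SD 4 | SD 5 | SD 6 |
|---|---|---|---|
| 3 points (all visits) | 0.99 | 0.93 | 0.82 |
| 2 points (none at week 10) | 0.82 | 0.64 | 0.49 |

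These figures use the SD of a single visit. A model that averages visits would be more precise, so the probabilities are not upper limits.

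*SST-Peer vs TAU.* Assume a social-communication effect of 0.35, none on thought challenging, and rho = 0.5. Then d_total = 0.35/1.732 = 0.20. At n = 67, power falls from 0.53 on the subscale to 0.21 on the total.

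**The case against.** The strongest reply is that the total measures what the article set out to measure. Its stated purpose covers social and cognitive content, and the cognitive component is what distinguishes CBSST from SST. If the question is which package conveys more, the total is a fair answer, and limiting the contrast to shared material asks a different question. This stands, and it is a reason to keep the total. It does not make the total informative about which arm teaches common skills better, and the article does not say which of the two meanings superior skill knowledge carries.

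A reader might infer that the CBSST-Peer vs SST-Peer result on the CMT is settled in advance. The documents do not support that. The Abstract says that the ability of peer specialists to deliver these structured treatments is unknown, so whether veterans will learn thought challenging from them is an open question. SST-Peer may gain enough on the social half to offset the difference. If the two modules run in sequence, the gap at week 10 may be small or absent, and that visit is pooled with the others. With d_tc = 0.5 the probability is only 0.39 at 67 per arm.

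The description of the CMT as tied to both interventions is loose rather than false, since its social half does relate to both. The social subscale is not fully neutral either: it was written to the CBSST module, and SST covers only some of the same skills.

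Finally, subscale reporting is often left to an analysis plan that is not shown. The article, however, does more than stay silent: it commits to the total.

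**Conclusion.** The concern holds as a problem of interpretation on a secondary outcome. Following the article as written, a significant CBSST-Peer vs SST-Peer difference on the CMT could arise entirely from material withheld from one arm, and the total could mask an SST-Peer advantage on social communication. That the score is built this way follows directly from the text. How much it would move the result is not known. Every probability shown rests on assumed effects, SDs and correlations, and they run from 0.17 to 0.99 at 67 per arm when the arms do not differ on social communication. The ILSS is the primary outcome and the basis of the power statement, so the trial's main conclusion is not touched.

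**What to change.** - Keep the 22-point total, described as a measure of uptake of the CBSST package.
- Prespecify separate analyses of the two 11-point subscales for all three contrasts.
- Base any conclusion about shared skill learning, for CBSST-Peer vs SST-Peer and for SST-Peer vs TAU, on the social communication subscale. State that this subscale was written to the CBSST module.
- In CBSST-Peer vs SST-Peer, interpret the thought-challenging subscale as a check that the cognitive content was learned.
- Amend the sentence under Patient outcomes to say that only the social half of the CMT is tied to both interventions.

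Table 1 gives each part its own maximum, so no new data should be needed. The cost is two extra secondary analyses and a possibly less favourable CBSST-Peer vs SST-Peer result. The article states that data analysts are blinded, so the change can be made before treatment codes are revealed.

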**Self-report measures**	
**Defeatist Performance Attitude Scale (DPAS)**	The DPAS is a 15-item, 5-min self-report subscale of the commonly used 40-item Dysfunctional Attitude Scale (DAS) derived from factor analysis. The DPAS indexes defeatist attitudes about one’s ability to perform tasks [23].
**Independent Living Skills Survey (ILSS) – primary outcome**	The ILSS [24] is a self-report measure of everyday functional living skills for patients with SMI that has proven to be reliable, stable, sensitive, and valid in multiple samples. The 51-item yes-no questionnaire takes less than 10 min to administer and assesses whether or not specific functioning behaviors have been performed over the past month.
**Patient Activation Measure (PAM)**	Patient activation is a self-report measure that refers to the knowledge, skills, confidence, and attitudes patients have for managing health and treatment. The shortened PAM is a 5-min,13-item measure in which respondents endorse items (e.g., “I know what each of my prescribed medications do”) on a scale from 1 (“disagree strongly”) to 4 (“agree strongly”) [25].
**Psychosocial Rehabilitation (PSR) Toolkit**	The PSR Toolkit [22] is a 10-min interview used to collect information on employment, educational activity, and residential situation. In this brief interview, status in each functioning domain is rated on a progressive scale, ranging from the absence of meaningful functioning in the domain to fully independent functioning.
**Recovery Assessment Scale (RAS)**	The RAS [26–28] is a 10-min checklist that assesses aspects of recovery with a special focus on hope and self-determination. The RAS has 41 items on which respondents rate themselves using a 5-point scale ranging from 1 = strongly disagree to 5 = strongly agree. The RAS is intended for use and has been tested with patients with SMI who receive services in outpatient settings and in peer-run programs.

**Table 2 Tab2:** Study outcomes

Domain	Specific measurement	Specific metric	Method of aggregation	Time points
Everyday functioning	Independent Living Skills Survey (ILSS)	Difference in the change from baseline to each follow-up time point, between the three study groups	Mean	Baseline, 10 weeks, 20 weeks, 32 weeks

#### Fidelity

Two measures will be used to assess fidelity for CBSST-Peer and SST-Peer group sessions: Cognitive Therapy Rating Scale for Psychosis (CTS-Psy) [29] and the Social Skills Training Fidelity Scale (SSTFS) [30]. Both are observation checklists that have been used extensively to evaluate fidelity for CBSST and SST [11]. CBSST-Peer and SST-Peer sessions will be audio-taped and 20% rated for fidelity using these measures.

### Data collection, data entry, and data management

#### Study interview data

Trained RAs collect data during four assessments at weeks 0 (baseline), 10 (mid-intervention), 20 (end-of-intervention), and 32 (3-month post-intervention follow-up). All data will be maintained in the database using the internal data management tools. The database has been established in such a way that data entry errors (out of bound values) or fields accidentally left blank are immediately flagged. Veterans will be compensated up to $170 (baseline, $25; 10 weeks, $35; 20 weeks, $55; 32 weeks, $55) for completing the study visits.

Data will be kept behind the VA firewall or in locked file cabinets. Identified data will be shared only with regulatory agencies or for patient safety. De-identified data will be shared in compliance with the VA guidelines. Multiple attempts will be made to collect study data from enrolled participants. The study staff will monitor the participants for adverse events in multiple ways. Participants in the two intervention groups will be in close contact with peer specialists, who will report any adverse event they observe. Usual treatment participants will be observed during the four assessment visits and by contact with the participant’s assigned clinical providers.

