**Methods:**

This study is a randomized, hybrid 1, research assistant-blinded, superiority trial. A total of 252 veterans with SMI will be recruited and randomized to one of three arms: CBSST-Peer vs. SST-Peer vs. treatment as usual. Participants randomized to CBSST-Peer or SST-Peer will participate in a 20-week group-based intervention that meets weekly for a 60-min class. All participants will complete 4 study assessments at baseline, 10 weeks, 20 weeks, and 32 weeks. A multidimensional battery of functional outcomes will be used with the Independent Living Skills Survey (ILSS) as the primary outcome measure. Post-study completion, veterans who participated in the CBSST-Peer or SST-Peer arms will randomly be invited to participate in focus groups, and peer specialists will complete interviews to further assess the effectiveness of each intervention.

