### Randomization procedures and rationale

Once veterans are enrolled and have completed the baseline assessment, block randomization will be performed using a computer-generated list of numbers with a centralized web-based database system (Daciforms; Dacima Software Inc., Montreal, QC). RAs will use the database, set on the blinded status, to randomize enrolled participants once all prescreening information has been entered. Although veterans and the peer specialists will know to which condition the veterans have been assigned, RAs responsible for all assessments will be blinded to the study treatment assignment to prevent bias with subjective data collection measures in subsequent assessments. Data analysts will also be blinded.

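### Adverse events are described as reaching the study through different sources in the class arms and in TAU, so class-arm versus TAU counts would mix treatment with opportunity to observe

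*Protocol article*

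**What the plan says.** The relevant text is in the protocol article, under Data collection, data entry, and data management (Study interview data). It opens generally: "The study staff will monitor the participants for adverse events in multiple ways". It then takes the arms separately. For the two class arms: "Participants in the two intervention groups will be in close contact with peer specialists, who will report any adverse event they observe". For TAU: "Usual treatment participants will be observed during the four assessment visits and by contact with the participant’s assigned clinical providers".

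Three other statements bear on this:

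- The visits are common to all arms. The abstract says: "All participants will complete 4 study assessments at baseline, 10 weeks, 20 weeks, and 32 weeks".
- Research assistants run those visits, and Randomization procedures and rationale says: "RAs responsible for all assessments will be blinded to the study treatment assignment". The same section makes clear that peer specialists know the allocation.
- Usual care continues in every arm (Participant eligibility; CBSST-Peer condition), so class-arm veterans also have clinicians who could report events.

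**The concern.** The sources named for the class arms and for TAU differ in three respects: who observes, how often, and whether the observer knows the allocation. If the text is followed as written, an event has a different chance of being recorded in a class arm than in TAU, even when the treatments are equally safe. A table of events by arm would then show a difference, or hide one, for reasons unrelated to treatment.

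There is also a coverage question within the class arms. Peer specialists can report only what they see, so their reporting depends on attendance and loses its scheduled basis when classes end. A veteran who stops attending, or who is in the follow-up period, is outside the one source named for that arm. Under Trial oversight, the only external reporting described is the annual report to the funder and the IRB, so events that no source picks up would not reach that report.

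**Working it through.** The article states no adverse-event rate, safety sample size or safety test, so there is no figure to reproduce. The check is a comparison of the text, followed by an illustration on stated assumptions.

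**1. Named sources and scheduled occasions after randomization**

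Randomization follows the baseline assessment, so the baseline visit cannot detect a post-randomization event. That leaves 4 − 1 = 3 visits per arm.

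| | CBSST-Peer, SST-Peer | TAU |
|---|---|---|
| Source named for the arm | Peer specialists | Assessment visits and contact with usual clinicians |
| Observer's knowledge of allocation | Known | Research assistants blinded; not stated for clinicians |
| Scheduled occasions, weeks 0–20 | Up to 20 classes | Visits at weeks 10 and 20; clinician contact, frequency not stated |
| Scheduled occasions, weeks 20–32 | No classes described | Visit at week 32; clinician contact, frequency not stated |

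The visits at weeks 10, 20 and 32 also take place in the class arms, but the adverse-event text names them only for TAU. Because the frequency of clinician contact is unknown, no total can be given for TAU and no ratio of occasions can be formed. For 32 − 20 = 12 weeks, the class-arm source has no scheduled contact behind it.

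**2. Size under assumed detection**

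Let p be the true share of participants with an event, equal in both arms, and let s₁ (class arm) and s₀ (TAU) be the probabilities that it is recorded. The observed shares are p·s₁ and p·s₀, so the observed risk ratio is s₁/s₀ whatever p is. The values of s₁, s₀ and p are assumptions; none comes from the article.

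- 0.9 / 0.9 = 1.00
- 0.9 / 0.7 = 1.29
- 0.9 / 0.5 = 1.80
- 0.7 / 0.9 = 0.78

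**3. Chance of a spuriously significant difference**

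With 252 / 3 = 84 per arm, no losses, and a two-sided 5% comparison of two proportions, the chance of significance in the direction of the detection gap is Φ[(|a − b| − 1.96·SE₀) / SE₁]. Here a = p·s₁, b = p·s₀, SE₀ is the pooled and SE₁ the unpooled standard error. For p = 0.20 and 0.9 versus 0.7: a = 0.18, b = 0.14, SE₀ = 0.0566, SE₁ = 0.0565, giving Φ(−1.25) = 0.105.

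| Detection, class arm vs TAU | p = 0.20 | p = 0.30 |
|---|---|---|
| 0.9 vs 0.9 | 0.025 | 0.025 |
| 0.9 vs 0.7 | 0.105 | 0.146 |
| 0.9 vs 0.5 | 0.320 | 0.480 |
| 0.7 vs 0.9 (TAU higher) | 0.105 | 0.146 |

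The reference value is 0.025 per direction. With equal detection in every arm, the observed ratio returns to the true one.

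**The case against.** The strongest reply is that this passage describes participant protection, not a comparative safety endpoint. Adverse events are not among the measures or study outcomes, and the analysis section announces no between-arm safety test. The article also condenses a fuller protocol, which may contain a common adverse-event form. That stands as a limit on the weight of the point. It does not remove it, because the point rests on what the article states about sources by arm and not on something left out.

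A reader might infer three stronger claims that the documents do not support:

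- **That safety cannot be compared between arms at all.** CBSST-Peer and SST-Peer share the same named source and can be compared with each other. The visits and usual clinicians exist in all three arms, so a common source is available.
- **That the counts are biased against the class arms.** Weekly classes make this plausible up to week 20. However, clinicians may detect some events that a group leader would not, and after week 20 the class-arm source weakens while those named for TAU continue. The direction is open.
- **That blinded research assistants carry out a TAU-only event check, and so must know the allocation.** The text does not say that visit observation is confined to TAU, that visits run differently by arm, or who contacts the clinicians. The TAU sentence can be read as listing what remains when there is no peer contact. Research assistants who observe everyone need no knowledge of allocation, so the two sections are compatible. At most the wording leaves a doubt that one sentence would settle.

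**Conclusion.** The point holds in a limited form. As written, adverse events are ascertained through different sources in the class arms and in TAU, so any class-arm versus TAU count mixes treatment with opportunity to observe. The direction is uncertain and may change when classes end at week 20.

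The size cannot be derived from the article. The ratios of 0.78 to 1.80 show only what plausible-looking detection gaps would do, and they rest entirely on the assumed detection probabilities. The significance figures also assume 84 per arm without losses and a test that the article does not announce.

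The primary ILSS analysis is untouched, and no breach of assessor blinding is shown. The change is worth making because it improves both comparability and safety coverage at very little cost.

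**What to change.** Have the research assistants put the same short adverse-event enquiry to every participant in all three arms at weeks 10, 20 and 32, and state that it does not depend on allocation. That statement also settles any doubt about consistency with the blinding described under Randomization procedures and rationale.

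Base any by-arm adverse-event summary on this common source alone. Keep peer-specialist and clinician reports for real-time safety response, and list them separately by source.

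The cost is one short form and a few minutes at each of three visits that are already held. A uniform record check by unblinded staff would be a further step, but the article describes record review only for recruitment and eligibility and identifies no such staff, so the fix does not rely on it.
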